### 4.4 Sample size calculation

The number of eligible subjects was calculated according to Campbell et al. (2004) for cluster randomized trials(35). The total number of subjects depends on the mean cluster size and the correlation between the clusters, known as the intracluster (or intraclass)

correlation coefficient. The intraclass correlation coefficient is the proportion of the total variance on the outcome, explained by the variance between the clusters. The sample size needs to be corrected for the design effect, to calculate the power of the cluster randomized trials.

To calculate the sample size, we used an intraclass correlation coefficient of 0.04(36,37) and a minimum of 20 patients per health care center. Additionally, we assume a minimal clinical detectable change of >10 points in the sum score of physical functioning of the RAND-36 questionnaire(38), and a standard deviation of 23.8(16). Based on these assumptions and the assuming power of 80%,  $\alpha=0.05$ , at least 10 health care centers and overall 206 participating patients are needed. With an expected drop-out rate of 20% a total of 248 participating patients (per arm 124 patients) are needed.

The feasibility is checked with the average number of patients with moderate MUPS per primary care practice (54 patients; based on the numbers of Julius Primary Care Network) and the expected response (40%). Consequently, the estimation is that we can include 21 patients per health care center and at least 12 health care centers need to participate in the study to obtain the total number of participating patients. Co-applicants Leidsche Rijn Julius Gezondheidscentra and Stichting Gezondheidscentra Eindhoven (together 15 health care centers) are already willing to participate. Therefore, our expectation is that the feasibility is sufficient.

[figure not shown]

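### The 206 patients in 10 centres stated for 80% power do not follow from section 4.4's own inputs, which give about 314 patients in 16 centres

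*Protocol*

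**What the plan says.** Section 4.4 of the protocol bases the trial size on the RAND-36 physical functioning score. The difference to detect is just over 10 points, the SD is 23.8, power is 80% and alpha is 0.05, with no statement of one or two sides. For clustering, the authors write "we used an intraclass correlation coefficient of 0.04(36,37) and a minimum of 20 patients per health care center". They accept that "The sample size needs to be corrected for the design effect", but print no value for the design effect. The conclusion is "at least 10 health care centers and overall 206 participating patients are needed".

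A 20% drop-out allowance raises this to 248 patients, 124 per arm. The feasibility paragraph then expects about 21 patients per centre and at least 12 centres, and reports that 15 centres are already willing. No baseline adjustment or gain from repeated measurements is listed among the inputs.

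**The concern.** All the inputs for a standard cluster-trial calculation are printed in one paragraph, so the result can be checked directly. Going from 178 unclustered patients to 206 is an inflation of about 16%. An intraclass correlation of 0.04 with 20 patients per centre calls for 76%. If the correction was not carried out as described, the recruitment target of 248 rests on a wrong figure. The trial would then have clearly less than 80% power for the difference that the protocol itself treats as the smallest worth detecting.

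**Working it through.** **Inputs, all from section 4.4 unless marked.** Difference d = 10; SD = 23.8; power 80%; alpha 0.05, two-sided (assumed); ICC = 0.04; cluster size m = 20; equal arms.

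**Unclustered size.** n per arm = 2 × (1.96 + 0.8416)² × 23.8² / 10² = 88.9, so 89 per arm and 178 in total.

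**Design effect.** DE = 1 + (m − 1) × ICC = 1 + 19 × 0.04 = 1.76.

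**Clustered size.** 178 × 1.76 = 313.3, so 314 patients; 313.3 / 20 = 15.7, so 16 centres.

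**Trying to reproduce 206.**
- Implied inflation: 206 / 178 = 1.16. At m = 20 this needs an ICC of 0.16 / 19 = about 0.008, a fifth of the stated 0.04.
- One-sided alpha 0.05: 71 per arm, 142 × 1.76 = 249.9, so 250. This is not 206 either.
- Putting 5 in place of 20: DE = 1 + 4 × 0.04 = 1.16, and 177.8 × 1.16 = 206.3. Five is the number of centres per arm when there are 10. This was the only variant tried that returned 206, and it is not a valid formula.

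**Power under the section 4.4 inputs, unadjusted comparison at one time point.** SE = SD × √(4 × DE / N). Normal power = Φ(10/SE − 1.96). The t version uses the noncentral t with (centres − 2) degrees of freedom.

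| Design | m | DE | SE | 10/SE | Normal | t |
|---|---|---|---|---|---|---|
| 248 recruited, 20% lost: 198 in 12 centres | 16.5 | 1.62 | 4.31 | 2.32 | 64% | 55.5% (10 df) |
| All 248 evaluable, 12 centres | 20.7 | 1.787 | 4.04 | 2.48 | 70% | 61% (10 df) |
| 206 in 10 centres | 20.6 | 1.784 | 4.43 | 2.26 | 62% | 51% (8 df) |

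The first row uses 198 because 248 × 0.8 = 198.4. The protocol's 248 is 206 × 1.2, which does not leave 206 after a 20% loss.

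**Difference detectable with 80% power.** For 206 in 10 centres: (1.96 + 0.8416) × 4.43 = 12.4 points (normal) or 14.2 (t, 8 df). For 198 in 12 centres: 2.8016 × 4.31 = 12.1 (normal) or 13.4 (t, 10 df).

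**The 314 on the same t basis.** With 16 centres and 14 df its power is about 75%, so 314 is itself a normal-theory figure and somewhat low.

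**Effect of baseline adjustment.** This assumes a baseline/follow-up correlation r, variance multiplied by (1 − r²), and the ICC unchanged. For 198 in 12 centres:
- r = 0.5: SE = 4.306 × 0.866 = 3.73; power 76.5% (normal) or 68% (t).
- r = 0.6: SE = 4.306 × 0.8 = 3.44; power 83% (normal) or 74% (t).

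**The case against.** The best counter-argument is that section 4.4 does not describe the analysis that will be run. Section 10.1 plans longitudinal mixed models corrected for potential confounders, and Table 1 collects the RAND-36 at baseline, 3 and 12 months. If baseline enters the model, precision improves. At a correlation of about 0.58, 206 patients would be enough by normal theory with a design effect of 1.76. This part stands. A reader might infer from the table that the trial's real power is 62% or 51%, and the documents do not support that. They give neither the correlation nor how baseline enters the model, so actual power is unknown. The figures above are what section 4.4's inputs imply for an unadjusted comparison.

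Three further points also stand. Ten centres is a stated minimum, and the feasibility plan has 12, so the 12-centre row is the fairer summary. Two-sided testing is an assumption, although one-sided testing does not rescue 206. The choice of degrees of freedom may be left to the statistical analysis plan, so the t-based figures are supplementary.

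None of this reconciles the printed number with the printed inputs. Section 4.4 claims no gain from adjustment, and its difference is anchored at 10 points, not at the 12 or so that 206 would support. That 5 was used in place of 20 is an inference from a close numerical match; the protocol does not show its formula.

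**Conclusion.** The stated sample size is wrong on its own terms. The section 4.4 inputs give about 314 patients in 16 centres by normal theory, not 206 in 10. Without baseline adjustment, the planned 12-centre design with 20% loss has about 64% power for 10 points (55.5% with 10 df). The 10-centre minimum has about 62% (51% with 8 df). This rests on two-sided alpha, equal cluster sizes and the stated ICC and SD. The finding that 206 does not follow depends neither on the degrees of freedom nor on sidedness.

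A reader might also infer that the trial must now recruit 314 patients, or could cheaply recover power by spreading the same patients over all 15 willing centres. Neither follows. Sixteen centres is more than the 15 willing, and baseline adjustment may close much of the gap. Spreading 206 patients over 15 centres means about 14 per centre against the stated minimum of 20. Centres are randomised before patients are selected (section 8.2), and section 8.3 speaks of remaining patients still to be approached, which suggests that recruitment was already under way.

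**What to change.** Rewrite the calculation in section 4.4. State whether alpha is two-sided, print the design effect (1.76 at 20 per centre) and the centre-level degrees of freedom, and give the power that follows for the planned 12 centres after drop-out, or the difference detectable with 80% power. Remove the claim of 80% power for 10 points.

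In section 10.1, declare that the primary RAND-36 mixed model adjusts for the baseline RAND-36 score. If this gain is used in the power statement, give the assumed correlation and its source. At 0.5 to 0.6, 198 completers in 12 centres would have about 77% to 83% power (normal) or 68% to 74% (t). This improves matters, but does not secure 80% on the t basis.

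The cost is one rewritten paragraph, one added sentence and a less favourable stated power. It needs no new patients, centres or measurements.

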## 4. STUDY POPULATION

### 4.1 Population (base)

In this study, 248 subjects with moderate MUPS from primary health care centers will be recruited.

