### 8.5 Replacement of individual subjects after withdrawal

Subjects who withdraw will not be replaced.

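### The 20% drop-out allowance in Protocol section 4.4 is applied as 206 × 1.2 instead of 206 / 0.8, so 248 recruits leave about 198 patients, not the stated 206; the power effect of this step alone is small

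*Protocol*

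**What the plan says.** Protocol section 4.4 takes a "minimal clinical detectable change of >10 points in the sum score of physical functioning of the RAND-36 questionnaire", "a standard deviation of 23.8", an intraclass correlation of 0.04 and at least 20 patients per centre. With power of 80% and alpha of 0.05 it concludes that "at least 10 health care centers and overall 206 participating patients are needed". The next sentence adds the allowance for loss: "With an expected drop-out rate of 20% a total of 248 participating patients (per arm 124 patients) are needed".

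The 248 is then used in two places. Section 4.1 makes it the recruitment target: "248 subjects with moderate MUPS from primary health care centers will be recruited". The feasibility paragraph of section 4.4, assuming 21 recruits per centre, concludes that "at least 12 health care centers need to participate in the study"; the same paragraph says that 15 centres are already willing.

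Section 8.5 closes off one way of making up losses: "Subjects who withdraw will not be replaced".

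**The concern.** The two sentences in section 4.4 do not fit together. The first says how many patients are needed for the intended power; the second is meant to say how many to recruit so that this number remains after 20% are lost. No section defines the 20% as anything other than a share of the recruited patients. Adding 20% to the required number is not the same as allowing for a loss of 20% of the recruited number, and it always gives too few.

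At stake are the truth of a stated sample-size figure that recurs as the recruitment target, and whether the minimum number of centres derived from it is enough. Because withdrawn patients are not replaced, the shortfall would remain in the data.

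**Working it through.** **Inputs, all from Protocol section 4.4:** required number 206 (103 per arm); drop-out 20%; recruited number 248 (124 per arm); difference 10; SD 23.8; intraclass correlation 0.04; 10 centres tied to the 206, and at least 12 planned; 21 recruits per centre. The section does not say whether alpha is one- or two-sided; two-sided 0.05 is assumed below.

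**Reproducing the plan's figure.** 206 × 1.2 = 247.2, rounded up to 248. Per arm, 103 × 1.2 = 123.6, rounded up to 124. Both printed figures are matched exactly.

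**The allowance applied to recruited patients.** N / (1 − d) = 206 / 0.8 = 257.5, so 258 (129 per arm).

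**What 248 delivers.**
- Retained at 20% loss: 248 × 0.8 = 198.4, about 198, which is 8 below 206.
- Loss that 248 can absorb while keeping 206: 1 − 206/248 = 16.9%.

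**Centres.** 248 / 21 = 11.8, hence 12. 258 / 21 = 12.3, hence 13. Filling all 12 × 21 = 252 places does not close the gap either: 252 × 0.8 = 201.6.

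**Effect on power.** With m = N/K patients per centre, the design effect is DE = 1 + (m − 1) × 0.04 and the effective number is N/DE. Power is Φ(10 / (23.8 × √(2/n)) − 1.96), where n is half the effective number. This normal approximation takes equal centre sizes and no baseline adjustment.

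| Patients with data | Centres | m | DE | Effective N | Power |
|---|---|---|---|---|---|
| 206 | 10 | 20.6 | 1.784 | about 115 | 61.7% |
| 206 | 12 | 17.2 | 1.647 | about 125 | 65.2% |
| 198.4 | 12 | 16.5 | 1.621 | about 122 | 64.2% |

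At 12 centres, the drop from 206 to 198 costs 65.2 − 64.2 = about 1 percentage point.

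**Why none of the rows is near 80%.** For individual randomisation, n per arm = 2 × (23.8 × (1.960 + 0.842) / 10)² = 88.9, so 89, or 178 in total. With 20 per centre, DE = 1 + 19 × 0.04 = 1.76, and 178 × 1.76 = 313.3, so about 314. The stated 206 does not follow from the stated inputs. That is a separate and larger matter, but it limits what correcting the drop-out step can achieve.

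**The case against.** The strongest reply is that a headcount misjudges a cluster trial. The 206 is tied to 10 centres, while recruitment is planned over at least 12. Spreading patients over more centres lowers the design effect, so 198 patients in 12 centres carry more information (effective number about 122) than 206 in 10 (about 115). This stands. A reader might infer from the shortfall of 8 that the drop-out step leaves the trial materially underpowered; the protocol's own intraclass correlation and centre numbers do not support that.

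It can also be said that treating each drop-out as wholly lost is a worst case. Section 10 plans intention-to-treat analysis with multiple imputation, section 10.1 a longitudinal mixed analysis, and section 8.6 asks patients who stop treatment to complete follow-up. Patients lost after the three-month measurement would still contribute. This too stands as a limit on the size of the loss. It does not justify multiplying by 1.2: imputation does not restore the information in outcomes never observed, and the allowance exists precisely to leave 206 patients with data.

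On centres, a reader might infer that recruitment is no longer feasible. The documents do not support that either. The thirteenth centre arises only because 54 × 40% = 21.6 is cut to 21; at 21.6, 12 centres give 259. The 12 is stated as a minimum, and the 15 willing centres offer 15 × 21 = 315 places.

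**Conclusion.** The concern holds as an arithmetic error in a stated figure. At the plan's own 20% loss, 248 recruits leave about 198 patients, 8 fewer than the 206 declared necessary, and 248 covers only about 17% loss. This rests on reading the 20% as a share of recruited patients, the ordinary meaning and the only one the protocol offers.

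The consequence for power is small: about 1 percentage point with 12 centres at an intraclass correlation of 0.04, and less if partial follow-up is used.

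A reader might infer that 258 is the corrected sample size. It is not. It is only the correct inflation of 206, and 206 gives about 62% power in 10 centres and about 65% in 12 on the stated inputs. Nearly all of the gap between about 64% and 80% comes from the base figure, not from the drop-out step. The power values assume a two-sided alpha of 0.05, equal centre sizes and no gain from baseline adjustment.

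**What to change.** In sections 4.1 and 4.4, keep 248 but state what it delivers: about 198 patients at 20% loss, or 206 at about 17% loss. Restate the power for about 198 patients over the planned 12 or more centres from the stated SD, difference and intraclass correlation (about 64% with 12 centres), and say that this differs from 80% mainly because of the base number.

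If the base number is revised, divide it by 0.8 and do not multiply by 1.2. The difference grows with the base: for 314, the two routes give 314 / 0.8 = 392.5, so 393, against 314 × 1.2 = 376.8, so 377. If 258 is quoted at all, label it as 206 inflated for 20% loss, without a claim of 80% power. At 21 per centre it would need 13 centres, which the 15 willing centres cover.

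Correcting the drop-out statement costs wording only. Recruiting to keep 206 would cost 258 − 248 = 10 more patients.

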**Figure 2 PRESUME screening method**

## 5. TREATMENT OF SUBJECTS

The PARASOL intervention is a blended multidisciplinary primary care intervention of the physical therapist and mental health nurse. The intervention is developed according to the literature and focus groups with experts (general practitioners, physical therapists, mental health nurses and psychologists). The aim of the intervention is to decrease severity and impact of symptoms, to improve quality of life in patients with moderate MUPS and to prevent chronic MUPS by providing insight in factors that may adversely affect prognosis, encouraging self-management as well as an active lifestyle. The focus of the intervention is on modifiable prognostic risk factors for the development of chronic MUPS(1,3,27). The intervention is constructed according to the principles of the modified consequence model(28), central sensitisation(25), cognitive behavioural approach(29-31) and graded activity(32-34).

### 5.1 Investigational treatment

#### A. Active face-to-face treatment

The intervention will take 12 weeks with 8-10 treatment sessions, 4-5 sessions per discipline (intake, week 1, 3, 6 and 12). Both the physical therapist and the mental health nurse will have thirty minutes per session. During the intake at both health care professionals, the complaints, treatment demand and negative or maintaining factors of the patient will be identified according to the SCEGS(3). The physical therapist will start with focussing on physical functioning (exercise, stress, pain and fatigue). In the next step the mental health nurse will gradually incorporate psychological and social functioning in the treatment plan. Both health care professionals will integrate cognitive behavioural principles in their part of the intervention. The last session in week 12 will only be with the physical therapist. In this last session, the intervention will be evaluated and long-term goals will be discussed (see Appendix 2 for a schematic view of the PARASOL intervention).

#### A1 Physical therapy

The Dutch multidisciplinary guideline for MUPS recommends active physical therapy (e.g. exercise therapy)(3,4). In advance, we will start with education regarding the unexplained symptoms. Education according to the sensitisation model of Nijs and van Wilgen is of interest due to the somatic fixation and anxiety for a severe disease of the subject(25). Concurrently, graded activity will be used to expand activities gradually(32-34). The graded activity schedule can be performed in daily life. In this way, we will focus on

perception and acceptance of physical complaints of the subjects during the face-to-face sessions.

## A 2 Mental health care

Besides physical therapy, the Dutch multidisciplinary guideline for MUPS and Somatoform Disorders and the MUPS standard of the Dutch college of general practitioners also recommend a referral to the mental health nurse(3,4). The mental health nurse can help the subjects in learning coping strategies according to the consequence model and operant conditioning, with the focus on changing perception and acceptance(39,40).

## B. Self-management/Home exercises

The face-to-face intervention will be integrated with eHealth modules, called blended health care(41). With this blended health care, we will reduce the burden for subjects with less face-to-face sessions, promote self-management in the home environment for subjects and thus reduce health care costs. This blended health care is proven effective (42,43). The online part of the PARASOL intervention consists of exercises (instruction videos), information modules on self-management and educative themes (description and videos). The modules will consist of three components:

1. Graded activity, an activity-focused method with operant conditioning behavioural principles. The subject will perform a chosen activity to his/her tolerance level (i.e., until pain or fatigue drives them to stop; pain-contingent), while their performance is recorded in distance units or number of repetitions. After at least three measurements, occurring over several days, baseline is determined and the chosen activity will be increased gradually (time-contingent)(44).
2. Videos of advised exercises
3. Videos and information on self-management and educative themes: central sensitisation, the consequence model, graded activity, behavioral change, stress, coping, relaxation, lifestyle advises, creating and performing an exercise plan and avoiding a relapse.

The content used for each individual subject will be selected according to the complaints.

## 5.2 Use of co-intervention

Not applicable

## 5.3 Escape medication

Not applicable. Patients are able to continue their regular medication.

## 6. INVESTIGATIONAL PRODUCT

Not applicable.

## 7. NON-INVESTIGATIONAL PRODUCT

Not applicable

## 8. METHODS

### 8.1 Study parameters/endpoints

#### 8.1.1 Main study parameter/endpoint

The primary parameters are adequate relief and quality of life. Adequate relief addresses symptoms improvement with a validated single question, scored on a dichotomous scale ("Over the past week have you had adequate relief of your symptoms?")(45,46). A responder for adequate relief is defined as a subject who will report adequate relief of their symptoms for at least 6 of the 12 weeks between T0 and T1, and for at least 3 of the 6 months between T1 and T2. Otherwise, a subject will be defined as a non-responder. Adequate relief can be seen as a clinically relevant endpoint at which the individual subject is satisfied with treatment(47). Quality of life will be measured with RAND-36 health survey. The RAND-36 is a valid and reliable self-reported questionnaire. The questionnaire consists of eight subscales; physical functioning, social functioning, role-physical or emotional problems, mental health, vitality, bodily pain and general health. A higher score (0-100) indicate a better quality of life(48,49).

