## SUMMARY

**Rationale:** Medically unexplained physical symptoms (MUPS) are a serious problem in primary care, with a spectrum from mild to moderate or chronic MUPS. The burden of chronic MUPS is substantial for patients, health care professionals and the society. Therefore, early identification of patients with moderate MUPS to prevent chronicity is needed. Recently a new screenings method with acceptable prognostic accuracy was developed using data from the electronic medical record of the general practitioner. Furthermore, we developed a proactive blended and multidisciplinary preventive intervention to reduce complaints of moderate MUPS and to prevent chronicity, called the PARASOL intervention.

**Objective:** The primary objective is to investigate the effectiveness of the PARASOL intervention on impact of symptoms and physical and mental dimensions of quality of life in patients with moderate MUPS compared with usual care.

Secondary objectives are to study:

- What is the influence of the PARASOL intervention on severity of symptoms, general health, physical behaviour, illness perception and self-efficacy in patients with moderate MUPS?
- What is the cost-effectiveness of the PARASOL intervention in patients with moderate MUPS?

**Study design:** Cluster randomized clinical trial

**Study population:** Patients with moderate medically unexplained physical symptoms, aged  $\geq 18$  years.

**Intervention:** The PARASOL intervention will take 12 weeks with 4-5 face to face sessions with the physical therapist and the mental health nurse as well as weekly online modules. The focus of the intervention is on modifiable prognostic risk factors of chronic MUPS, with integration of principles of the modified consequence model, central sensitisation, cognitive behavioural approach and graded activity.

**Main study parameters/endpoints:** The main study parameters are impact of symptoms and quality of life.

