## **2. OBJECTIVES**

Primary Objective:

What is the effectiveness of the PARASOL intervention on impact of symptoms and physical and mental dimensions of quality of life in patients with moderate MUPS compared with usual care?

Secondary Objectives:

1. What is the influence of the PARASOL intervention on severity of symptoms, general health, physical behaviour, illness perception and self-efficacy in patients with moderate MUPS compared with usual care?
2. What is the cost-effectiveness of the PARASOL intervention in patients with moderate MUPS compared with usual care?

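### The primary outcome set is defined inconsistently: the RAND-36 score and the time point are left open, and the stated 80% power covers physical functioning only

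*Protocol*

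**What the plan says.** The protocol describes its primary outcome in several places.

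- Section 2 (primary objective): "impact of symptoms and physical and mental dimensions of quality of life". This makes three components, and the objective in the Summary agrees.
- Summary (main study parameters): "The main study parameters are impact of symptoms and quality of life".
- Section 8.1.1: "The primary parameters are adequate relief and quality of life". Adequate relief is a dichotomous responder outcome. Quality of life is the RAND-36, described as follows: "The questionnaire consists of eight subscales; physical functioning, social functioning, role-physical or emotional problems, mental health, vitality, bodily pain and general health". No summary score is named and no subscale is put first.
- Table 1 in section 8.3: the instrument for impact of symptoms is the Adequate Relief question, and the instrument for quality of life is the RAND-36.
- Section 4.4: "we assume a minimal clinical detectable change of >10 points in the sum score of physical functioning of the RAND-36 questionnaire", with SD 23.8, alpha 0.05 and 80% power. No other outcome is sized.
- Section 3 and Table 1: follow-up at 3 and 12 months. Section 10.1 names longitudinal mixed analyses and gives no primary contrast or time point.

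**The concern.** The two constructs agree across sections, but the variable that stands for quality of life does not. In section 2 it is a physical and a mental dimension, neither tied to a score. In section 8.1.1 it is the whole questionnaire. In section 4.4 it is one physical score. With two follow-up times and no primary one, the protocol does not identify a single primary result or a fixed set of them.

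Two things are at stake. If the choice of score and time stays open until the data are known, the chance of at least one nominally significant primary result under no effect is well above 5%. And the outcome with a power statement need not be the one that is reported: a 10-point difference on a 0-100 scale says nothing about power for a dichotomous responder outcome or for a mental score.

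**Working it through.** **The plan's own figure.** Section 4.4 gives 206 patients before drop-out for a 10-point difference, SD 23.8, alpha 0.05, power 80%, ICC 0.04 and 20 patients per centre.

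- Unadjusted n per arm = 2 × (23.8 × (1.960 + 0.842) / 10)² = 88.9, so 89 per arm and 178 in total.
- Design effect = 1 + (20 − 1) × 0.04 = 1.76, and 178 × 1.76 = 313.

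The stated 206 does not reproduce. That is a separate sample-size matter. To keep it apart, the power figures below take the protocol's 80% at face value.

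**How many primary tests the text allows.** Adequate relief counts as one outcome. Quality of life counts as two (the dimensions in section 2) or eight (the subscales in section 8.1.1).

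| Reading | Two dimensions | Eight subscales |
|---|---|---|
| One overall treatment test per longitudinal model | 1 + 2 = 3 | 1 + 8 = 9 |
| RAND-36 tested at 3 and 12 months, one composite responder | 1 + 2×2 = 5 | 1 + 8×2 = 17 |
| Every outcome tested for both periods | 3×2 = 6 | 9×2 = 18 |

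The responder row is uncertain because the rule joins two periods: "for at least 6 of the 12 weeks between T0 and T1, and for at least 3 of the 6 months between T1 and T2". This can mean one composite responder or one responder per period.

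**Family-wise error** if each of k tests is done at two-sided 0.05, any success counts, and there is no effect. For independent tests it is 1 − 0.95^k. The correlated values come from 200,000 simulated draws of equally correlated normal statistics; the correlations are assumed, since the protocol gives none.

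| k | Independent | Correlation 0.5 | Correlation 0.7 |
|---|---|---|---|
| 3 | 14% | 13% | 11% |
| 6 | 26% | 21% | 16% |
| 9 | 37% | 27% | 20% |
| 18 | 60% | 40% | 28% |

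**Power after a split of alpha.** At 80% power and two-sided 0.05 the expected test statistic is 1.960 + 0.842 = 2.802. With a Bonferroni split over k tests, power = Φ(2.802 − z), where z is the two-sided critical value at 0.05/k.

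- k = 2: z = 2.241, Φ(0.561) = 71%.
- k = 3: z = 2.394, Φ(0.408) = 66%.

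Regaining 80% for the same effect means scaling 206 by the squared ratio of the z-sums:

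- k = 2: 206 × (3.083 / 2.802)² ≈ 250 before drop-out.
- k = 3: 206 × (3.236 / 2.802)² ≈ 275 before drop-out.

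These figures apply to physical functioning, or to another outcome with the same standardised difference. For adequate relief the protocol gives no control rate and no target difference, so its power cannot be derived from the document.

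**The case against.** The strongest reply is that the sections are closer than they look. Summary, objective, section 8.1.1 and Table 1 all name impact of symptoms and quality of life, and Table 1 maps the first to the Adequate Relief question. Sizing a trial on one component is common and does not declare a third primary. The sentence on eight subscales may only describe the instrument. A longitudinal mixed model can give one treatment test per outcome. Testing order and alpha allocation often sit in a statistical analysis plan, which is not at hand here.

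Much of this stands, and it rules out several stronger readings that a reader might infer:

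- That the protocol names three different primary outcomes. Table 1 shows that it does not; the mismatch lies in how quality of life is specified and in which outcome is sized.
- That it commits to 6 to 18 tests. It states no count, and 3 to 9 or 5 to 17 fit the text equally well.
- That any single success would count as a positive trial. The protocol writes no success rule, so the error rates above are conditional on that assumption.
- That splitting alpha over two outcomes cuts power from 62% to 51%. Those values follow from 206 patients at ICC 0.04 and carry the separate sample-size problem; from the stated 80% the split gives 71%.
- That physical functioning must become the sole primary. Section 8.1.1 names adequate relief first and regards it as clinically relevant; being used for sizing does not settle primacy.

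What the reply does not remove is the conflict in the protocol's own text. A later analysis plan would have to choose between sections 2, 4.4 and 8.1.1, because they do not say the same thing.

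**Conclusion.** The point holds in this form: quality of life is primary without an agreed score or time point, sections 2, 4.4 and 8.1.1 specify it in three ways, and alpha 0.05 with 80% power is set for physical functioning alone.

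Under the mildest reading (3 tests) the family-wise error would be two to three times the nominal 5%, and it rises with the number of tests. The figures for 18 independent tests are an upper end and not a plausible centre, since subscales of one questionnaire in the same patients are likely to be correlated. All error rates assume unadjusted testing at 0.05 with any success counting. The power figures assume that the stated 80% is correct for physical functioning. The absence of a multiplicity procedure is not itself the finding.

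**What to change.** Before outcome data are seen:

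1. State in sections 2, 4.4, 8.1.1 and 10.1, in the same words, which RAND-36 score or scores are primary and at which time point. Bring the Summary and Table 1 into line.
2. Choose one of two routes. Either designate one primary outcome and test the others in a fixed order after it, or keep adequate relief and the chosen RAND-36 score(s) as primaries with Holm control of the overall 0.05.
3. Label the remaining subscales and the other time point as secondary.
4. Say in section 4.4 that the 80% applies to physical functioning only, or give the power at the split alpha. If adequate relief stays primary, add its assumed control rate and difference.
5. State whether adequate relief is one composite responder or one per period.

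This needs wording and a short recalculation, but no new data collection. The price is that some outcomes lose the primary label, or that the stated power becomes less favourable (about 71% for two tests and 66% for three on the protocol's own 80%).
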